## Estimated sample size and power

Patients will be randomized in a 1:1 fashion. It is anticipated that the rate of the primary endpoint pCR will be approximately 30% in the control arm. We aim to increase the rate of pCR in the experimental arm to 40%, i.e. a 10 percentage points increase, which is regarded clinically relevant since it would translate into improved disease-related outcomes. With a power of 80% and an alpha of 5%, a total of 712 patients have to be included; 356 in each arm. Accounting for a drop-out of 10%, we aim to include 790 patients. Stratification at the moment of computerized randomization will be done based on site of treatment (hospital) and biological tumour subtype (ER+HER2-, ER+HER2+, ER-HER2+, ER-HER2-).

## Statistical analysis plan

All outcomes will primarily be analysed using an intention-to-treat approach, i.e. all study subjects will belong to the treatment group (exercise intervention or control) they were assigned to, disregarding compliance. As sensitivity analysis, all outcomes will also be analysed using a per-protocol approach, meaning that participants in the intervention group who comply with less than 65% of the prescribed physical exercise program or complete less than 40% of the planned neo-adjuvant systemic therapy (around two 3-weekly courses) will be excluded from analysis.

*Covariate adjustment in statistical models*

Guidelines from the European Medicines Agency (EMA) regarding statistics and covariate adjustments recommend that factors that are used to stratify the randomization, i.e. site of treatment and biological tumour type in this trial, should be accounted for in the statistical analysis^35,36^. However, it is also recognized that “limited numbers of subjects per centre will make it impracticable to include the centre effects in the statistical model”. In this trial it is very likely that some of the centres will contribute few patients, which may cause problems in some of the statistical models, in particular for the categorical outcomes (such as the primary endpoint, pCR) where the variability in the outcome may be too small within each site. Hence, the statistical models, described below, will primarily be adjusted for biological tumour type and not for study site. If appropriate and if the data allows (i.e. no convergence problems and not too small subgroups), the site effect will also be incorporated in the models as a random effect in the mixed models and as a fixed factor in the remaining logistic regression models.

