## Population

Clinically T1-3, N0-2 BC patients scheduled for NACT and surgery with curative intent and fulfilling all inclusion criteria and no exclusion criteria as listed below. Patients with oligometastases scheduled for such curative treatment are eligible. Baseline stratification is performed based on treating hospital and biological tumour subtype (ER+HER2-, ER+HER2+, ER-HER2+, ER-HER2-) prior to randomization.

Eligible patients are identified at pre-NACT multidisciplinary team conferences and then receive information about the trial by their oncologist or surgeon, avoiding undue delays. Informed consent is mandatory before randomization and can be obtained by physician or nurse with the appropriate delegation. All participants will undergo standardised tests of physical condition and strength before start of NACT and after NACT but before surgery.

| **Inclusion criteria** | **Exclusion criteria** |
| --- | --- |
| - Patients with primary invasive breast cancer cT1-T3 cN0-2 - Full tumour biology available before initiation of NACT (ER, PR, HER2, tumour grade, and Ki67) - Written informed consent - Age ≥ 18 years | - Bilateral invasive breast cancer - Pregnancy or breast-feeding - The presence of musculoskeletal, neurological, respiratory, metabolic or cardiovascular conditions that may prevent safe completion of the exercise and testing demands of the study - Currently performing equal to or more than 150 mins of moderate to high intensity aerobic exercise and 2 sessions per week of moderate intensity resistance exercise (WHO criteria) |

In case of pre-term abortion of NACT, participants may remain on the trial. Participants who have not received at least four treatment cycles (three weekly treatments of e.g. paclitaxel correspond to one treatment cycle) as NACT are excluded from per-protocol analyses (see statistical analysis plan).

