### Control

The aim of the trial is to compare the effects of an exercise program with routine care rather than to test a specific type of exercise. Thus, the control group is a routine care control group, which commonly implies brief verbal, general information about the benefits of physical activity from the treating physicians or breast cancer nurses. Participation in voluntary training groups organised by the treating hospital is not encouraged for participants since this implies that physical activity is potentially increased to the level specified in exclusion criteria. It is important to acknowledge that individuals consenting to an exercise trial may be more predisposed to exercising and may thus continue performing physical exercise if they are allocated to the control group. To measure this potential effect, all physical activity of both groups will be digitally collected so any “contamination” in the control group can be accounted for in the analysis. Importantly, the trial pursues an active recruitment strategy in order to meet potential participants at their respective fitness level however little they may be used to exercise. The control group will not have access to trial-specific exercises via the mobile application.

##

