3. Overall, breast cancer-specific and recurrence-free survival at 2, 5 and 10 years. For overall survival, censuring is at death or at date for latest follow-up. For breast cancer-specific survival, censuring is at breast cancer-specific death or at date of last follow-up. For recurrence-free survival, censuring is at first local, regional or distant recurrence or at death or date of last follow-up. Contralateral invasive or in situ breast cancer or non-breast secondary malignancies are not counted as an event, in accordance with STEEP criteria^32^.
4. Health-related quality of life including fatigue, assessed by the EORTC QLQ-C30 and BR23 questionnaires (baseline, pre-surgery, 1- and 2-year follow-up)
5. Self-reported physical activity (Modified Godin Leisure Time Physical activity questionnaire) at baseline, pre-surgery, and 1- and 2-year follow-up, facilitating subsequent adjustment for any cross-contamination in the control group
6. Toxicity-related outcomes:
   1. Chemotherapy completion rates, i.e. the proportion of participants receiving the planned number of treatments at full dosage regarding neoadjuvant chemotherapy (measured pre-surgery).
   2. Number of unplanned hospital admissions during neoadjuvant chemotherapy.
   3. Objective cognitive dysfunction measured by an online neuropsychological test (Amsterdam Cognition Scan)^33^ (baseline and 1-year follow-up).
   4. Cardiac toxicity (defined as either left ventricular ejection fraction (LVEF) decline >15% or LVEF decline below an absolute value of 50% or clinical heart failure), to be measured by echocardiogram at baseline and after 3 months of NACT in the HER2-positive subgroup
   5. Sick leave (patient-reported percentage of sick leave as a single measurement pre-surgery and at 1- and 2-year follow-up)
7. Device-measured physical activity level and resting heart rate assessed through the Fitbit activity tracker (baseline to 1-year follow-up).
8. Muscle strength assessed through the handgrip strength test and hypothetical 1-RM maximal leg muscle strength tests (baseline and pre-surgery).
9. Cardiorespiratory fitness assessed by the Ekblom-Bak submaximal cycle test (baseline and pre-surgery).

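### The protocol gives two incompatible per-protocol rules, and one of them, as worded, applies the chemotherapy criterion to the exercise arm only, which can bias that sensitivity analysis

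*Protocol*

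**What the plan says.** The protocol's Statistical analysis plan section fixes the hierarchy first: "All outcomes will primarily be analysed using an intention-to-treat approach". It then adds: "As sensitivity analysis, all outcomes will also be analysed using a per-protocol approach". The per-protocol exclusions that follow are for "participants in the intervention group who comply with less than 65% of the prescribed physical exercise program or complete less than 40" per cent "of the planned neo-adjuvant systemic therapy (around two 3-weekly courses) will be excluded from analysis". As the sentence is built, both the exercise criterion and the chemotherapy criterion belong to the intervention group. No exclusion is stated for controls.

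The protocol's Population section gives another rule. "Participants who have not received at least four treatment cycles" are left out of per-protocol analyses. No arm is named, exercise adherence is not mentioned, three weekly doses count as one cycle, and the reader is referred to the statistical analysis plan.

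**The concern.** Per-protocol is the stated sensitivity analysis for every outcome, pCR included. Two rules stand in one document, and the set cannot be built without choosing between them. The control group receives routine care without the app, so allocation is apparent to participants and staff, and an unresolved choice could end up being made once results are known.

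Following the Statistical analysis plan section literally creates a second problem. Participants with little chemotherapy leave the exercise arm but stay in the control arm. That is exclusion on a post-randomisation event in one arm, so the groups compared are no longer those formed by randomisation. The protocol's Background (Physical exercise and chemotherapy) ties full-dose completion to better prognosis and proposes better completion as a route to higher pCR. On that reasoning, the participants removed would tend to be those with poorer results.

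**Working it through.** **1. The plan's own figures.** Inputs from Estimated sample size and power: pCR 30% against 40%, 80% power, 5% alpha, 1:1 allocation; two-sided from the Primary endpoint section. With pooled variance,

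n = [1.96·√(2·0.35·0.65) + 0.8416·√(0.30·0.70 + 0.40·0.60)]² / 0.10² = (1.322 + 0.565)² / 0.01 ≈ 356 per arm, 712 in total.

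The stated sample size reproduces. It does not depend on the per-protocol set.

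**2. The two rules side by side.**

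| | Population section | Statistical analysis plan section |
|---|---|---|
| Chemotherapy threshold | fewer than 4 cycles | below 40% of planned, about 2 courses |
| Arms covered | none named, so both | intervention group |
| Exercise criterion | none | below 65% compliance |

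**3. Where the thresholds disagree.** The protocol does not give the number of planned cycles, so it is assumed here. The 40% gloss implies 2 / 0.40 = 5 courses. The Intervention section gives about five months to surgery, or 5 × 30.4 / 21 ≈ 7 three-week cycles.

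| Planned cycles (assumed) | 40% of planned | 4 cycles as share | Exercise-arm cycle counts classified differently |
|---|---|---|---|
| 5 | 2.0 | 80% | 2 and 3 |
| 6 | 2.4 | 67% | 3 |
| 7 | 2.8 | 57% | 3 |
| 8 | 3.2 | 50% | none |

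The last column is for participants who meet the 65% exercise criterion. At eight planned cycles the percentage rule and the four-cycle rule agree in whole cycles, but the gloss of about two courses no longer fits. A control participant with 0 to 3 cycles is out under the Population section and in under the Statistical analysis plan section, whatever number is planned.

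**4. Chemotherapy completion.** Anyone below 40% of planned therapy is by definition a non-completer. If completion is c in both arms and a share g is removed from the exercise arm alone, completion there becomes c / (1 - g), which exceeds c for any g above zero. The Background says at least a third of patients have dose reductions. Taking c = 0.667 and g = 5% (both assumed): 0.667 / 0.95 = 0.702, a shift of +3.5 points with no true effect.

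**5. pCR.** Set pCR to 30% in both arms, the planned control rate. Let f be the share of the exercise arm excluded and q their pCR. The crude shift is

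(0.30 - f·q) / (1 - f) - 0.30.

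The protocol gives neither f nor q; both are assumptions.

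| f | q | Retained pCR | Shift (points) |
|---|---|---|---|
| 5% | 5% | 0.2975 / 0.95 = 31.3% | +1.3 |
| 20% | 20% | 0.26 / 0.80 = 32.5% | +2.5 |
| any | 30% | 30.0% | 0 |
| 20% | 40% | 0.22 / 0.80 = 27.5% | -2.5 |

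The target effect is 10 points. If one chemotherapy rule covers both arms and exercise has no effect, the same share with the same pCR leaves each arm, and the chemotherapy part of the shift vanishes. The part due to the 65% exercise criterion remains.

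**The case against.** Several points on the other side are sound.

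- Intention-to-treat is primary for all outcomes, so the primary pCR test does not rest on this set.
- The words naming the intervention group could be meant for the exercise clause alone, with the Population section supplying the chemotherapy rule for everyone. That reading removes the one-arm chemotherapy exclusion. It goes against the grammar of the sentence, though, and leaves four cycles against about two unresolved.
- A separate statistical analysis plan may settle the matter. Both rules nevertheless stand in the protocol, which has a section with that title.
- An exercise criterion can only apply where exercise is prescribed, so its one-sidedness is unavoidable.

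A reader might infer that every per-protocol estimate is biased towards exercise. The protocol does not support that. Apart from chemotherapy completion, direction and size depend on who is excluded. Nothing in the protocol says that people who miss exercise sessions would have lower pCR if exercise had no effect. Published pCR in the Background runs from 10.8% to 63.7% by subtype, so the excluded group's subtype mix could move the crude rate either way. The planned model adjusts for subtype; the crude formula above does not.

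A reader might also extend the criticism to control-arm contamination, which the Control section says "can be accounted for in the analysis" and the outcome list describes as "facilitating subsequent adjustment for any cross-contamination in the control group". Neither place fixes a method, so there is no stated analysis to fault.

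**Conclusion.** The contradiction is established from the text alone: the rules differ in threshold, in arms covered and in whether exercise adherence counts. Taken as written, the one-arm chemotherapy exclusion can bias the per-protocol analysis, probably in favour of exercise, given the protocol's own link between completion and prognosis. For chemotherapy completion the upward push is mechanical. For pCR, the illustrations in the last table above run from -2.5 to +2.5 points, and both their size and their sign rest on assumed values.

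This should be corrected, but it is not critical to the trial: the intention-to-treat result and the sample size stand. The practical loss is that the planned sensitivity analysis cannot serve as independent support for the main result.

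**What to change.** 1. Reconcile the Population and Statistical analysis plan sections into one chemotherapy-exposure rule for the per-protocol set, with one threshold in one unit. No view is taken here on which threshold.
2. State that this rule applies identically to both arms.
3. State that the 65% exercise criterion can apply only to the exercise arm, so results using it are not a randomised comparison and cannot on their own corroborate the intention-to-treat result.
4. Optionally add, without replacing the per-protocol analysis, a complier-average effect estimate using randomisation as instrument. It answers a different question and needs its assumptions stated: a definition of compliance, and that allocation affects outcome only through the measured exercise.

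Items 1 to 3 cost wording in two sections and need no new data. Item 4 costs one further analysis and its specification. All of it should be settled before outcome data are examined by arm.

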#### Primary endpoint (pCR)

The primary outcome in this trial (pCR) is dichotomous, and will be assessed through histopathological examination of the surgical specimen after completed NACT. Hence, a multivariable logistic regression model, adjusting for biological tumour type (stratification factor in the randomization) will be used. The treatment effect will be assessed in terms of the resulting odds ratio between the two treatment arms together with a 95% confidence interval and a complementary Wald test. A two-sided statistical test with 5% significance level will be used. Furthermore, differences in pCR rates between the two treatment arms will be explored for each biological tumour type subgroup (ER+HER2-, ER+HER2+, ER-HER2+, ER-HER2-), using an interaction between treatment and biological tumour type.

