## Data management

All data are registered using an electronic Case Report Form (eCRF). Monitoring is performed according to Good Clinical Practice (GCP) guidelines. The eCRF provides data on age, demographics, background medical data, and initial tumour and lymph node characteristics deriving from clinical, radiological and histopathological assessment, details concerning type, dose and duration of neoadjuvant and adjuvant systemic therapy, as well as histopathological results at surgery and data on follow-up. Data are managed by the Clinical Trial Office at Centre for Clinical Cancer Studies, Karolinska University Hospital, Stockholm, Sweden. Security is comparable to bank security with encrypted data.

Recorded information is pseudonymised and the key kept at each responsible site. Keys may however need to be transferred to trial staff for quality assurance purposes such as central review of pathology slides and central review of imaging. Information is confidential and the database is privacy-protected; i.e., no data can be traced back to the patient in research reports and no unauthorized individuals may have access to the data about individuals in the database. The database will be maintained until further notice (at least 20 years after inclusion of the last patient) and be reported in accordance with General Data Protection Regulation (GDPR). The authority responsible for the database is Karolinska Institutet, Stockholm, Sweden.

The Neo-ACT trial is registered at www.clinicaltrials.gov (NCT05184582).

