#### Secondary endpoints

1. *Residual Cancer Burden (RCB)*

Residual Cancer Burden (RCB) is measured as four ordered categories (RCB-0 which corresponds to pCR, RCB-I, RCB-II, and RC-III) at histopathological assessment of the surgical specimen. An ordinal regression model, adjusting for biological tumour type (stratification factor in the randomization), will be used to analyse differences between the treatment arms. If the proportional odds assumption of the model is violated, a nominal regression model or a generalized logistic model will be used instead if appropriate.

1. *Objective tumour response*

Response Evaluation Criteria in Solid Tumours (RECIST) will be applied in order to assess change in radiological tumour size (%) from baseline to pre-surgery imaging. RECIST criteria classify response into four ordinal outcome categories: complete response, partial response, stable disease and progressive disease (see page 18)^31^. An ordinal regression model, adjusting for biological tumour type (stratification factor in the randomization), will be used to analyse differences between the treatment arms. If the proportional odds assumption of the model is violated, a nominal regression model or a generalized logistic model will be used instead if appropriate. Tumour size at histopathological assessment of the surgical specimen may be included in comparative analyses. Mean difference in reduction of tumour size between treatment arms will be analysed with an ANOVA, including biological subtype as a factor in the model.

1. *Survival outcomes*

All-cause, breast cancer-specific and recurrence-free survival will be analysed at 2, 5 and 10 years. Contralateral breast cancer is not regarded an event. Difference in time-to-event outcomes between treatment arms will be compared. The mortality outcomes are defined as time from date of randomisation to death (from any cause or breast cancer as underlying cause, respectively) or censoring at end of follow-up. For recurrence-free survival, the outcome is measured as time from date of randomisation to breast cancer relapse or censoring at end of follow-up. Survival estimates after 2, 5 and 10 years of follow-up will be compared using Kaplan-Meier estimates. Furthermore, a Cox regression model, adjusting for biological subtype will also be used.

1. *Health-related quality of life*

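### Free improvement, modest gain: the primary pCR model could also be adjusted for grade, Ki67, PR, cT and cN, which every participant has at entry

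*Protocol*

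**What the plan says.** Under Primary endpoint (pCR), the protocol specifies that "a multivariable logistic regression model, adjusting for biological tumour type (stratification factor in the randomization) will be used". The result is an odds ratio with a 95% confidence interval and a Wald test, and "A two-sided statistical test with 5% significance level will be used".

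The paragraph on covariate adjustment gives the reasoning. It cites European guidance on accounting for stratification factors, sets site aside as a primary covariate because some centres will be small, and allows site as a fixed factor in the logistic models if there are no convergence or subgroup-size problems. It does not discuss any other baseline predictor.

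The Population section requires "Full tumour biology available before initiation of NACT (ER, PR, HER2, tumour grade, and Ki67") and restricts entry to cT1-T3, cN0-2. The Data management section has the eCRF record "initial tumour and lymph node characteristics deriving from clinical, radiological and histopathological assessment". The study calendar places full tumour biology in the baseline block, ahead of randomisation.

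Subtype is likewise the covariate in the RCB and RECIST models, and for survival "a Cox regression model, adjusting for biological subtype will also be used".

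**The concern.** pCR is a binary outcome that may vary considerably between patients of the same subtype. If grade, Ki67, PR, stage or nodal status predict response within a subtype, a model that omits them leaves explainable variation unexplained, and the Wald test is somewhat less powerful than it could be. Randomisation is stratified by hospital and subtype only, so the arms may differ by chance on these features, and the planned model would not correct for that. Choosing covariates after seeing such an imbalance would be open to criticism; naming them now would not.

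At stake is a modest amount of power on the trial's single primary test. The data are already required for every participant, and the stated reason for caution about covariates (small centres) does not apply to them.

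**Working it through.** **1. The plan's own figure.** The section Estimated sample size and power assumes a control pCR rate of about 30% and a target of 40% with exercise, and concludes: "With a power of 80% and an alpha of 5%, a total of 712 patients have to be included; 356 in each arm". With pooled variance, two-sided 5% and no continuity correction:

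n per arm = [1.960·√(2·0.35·0.65) + 0.8416·√(0.30·0.70 + 0.40·0.60)]² / 0.10² = (1.322 + 0.565)² / 0.01 ≈ 356.

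This reproduces 356 per arm and 712 in total. Allowing for 10% drop-out, 712/0.9 ≈ 791, or 792 as an even total, against the stated 790; the difference is immaterial. The calculation is for an unadjusted comparison and counts on no gain from covariates.

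**2. Simulation set-up.**
- From the documents: pCR by subtype in the Background (10.8% ER+HER2-, 29.4% ER+HER2+, 63.7% ER-HER2+, 50.7% ER-HER2-) and about 30% HER2-positive (Secondary endpoints, cardiovascular toxicity).
- Assumed: the HER2-positive share splits 18%/12%. The triple-negative share then follows from 30% overall pCR: (0.30 − 0.18·0.294 − 0.12·0.637 − 0.70·0.108) / (0.507 − 0.108) = 0.238. That leaves 46.2% ER+HER2-.
- Also assumed: covariate distributions (grade 3 in 35% to 80% by subtype; cT1/2/3 in 20/60/20%; cN+ in 50%; Ki67 as a roughly standardised score) and their odds ratios within subtype.
- The treatment effect was set so that overall pCR is 30% against 40%. There were 4,000 trials per scenario.

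**3. Results at 712 patients**, subtype-only against subtype plus grade, Ki67, cT and cN. Odds ratios are in the order grade 3 / Ki67 per unit / cT step / cN+.

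| Assumed strength within subtype | Power | Log OR | SE of log OR |
|---|---|---|---|
| None | 88.2% → 88.4% | 0.566 → 0.569 | 0.180 → 0.182 |
| Weak (1.3/1.2/0.8/0.85) | 87.3% → 87.2% | 0.559 → 0.571 | 0.180 → 0.183 |
| Moderate (1.6/1.4/0.65/0.75) | 88.4% → 89.6% | 0.566 → 0.601 | 0.180 → 0.187 |
| Strong (2.5/1.8/0.5/0.55) | 88.3% → 92.9% | 0.562 → 0.660 | 0.180 → 0.197 |

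The Monte Carlo error of each power figure is √(0.88·0.12/4000) ≈ 0.5 point. The unadjusted model has about 80% power in all four rows, so subtype supplies most of the obtainable gain (about 8 points). At 790 patients the four rows become 90.7% → 90.7%, 91.7% → 92.3%, 91.2% → 92.4% and 90.9% → 94.4%.

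A separate simulation with five covariates, a subtype mix of 44.5/20/10/25.5% and a within-subtype prognostic SD of 0.5, 0.75 or 1.0 log-odds gave 88.1% → 89.6%, 87.9% → 91.2% and 87.8% → 92.2%. A run with eight added parameters and an SD from 0 to 1.0 gave a gain of roughly 0 to 4 points.

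**4. Type I error.** Under the null, subtype-only and fully adjusted models rejected in 4.8% and 4.7% of trials (no prognostic value) and in 5.2% and 5.2% (moderate). In the five-covariate simulation at SD 1.0, both rejected in 4.6%.

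**5. Where the gain comes from.** In the strong row z moves from 0.562/0.180 ≈ 3.12 to 0.660/0.197 ≈ 3.35. The standard error rises, but the conditional log odds ratio rises faster. The interval for the log odds ratio therefore does not narrow. A standardised pCR difference does become more precise: its variance fell by about 4%, 8% and 13% at SD 0.5, 0.75 and 1.0.

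**6. Chance imbalance.** For a prognostic score with unit SD, the difference in arm means has SD √(2/356) = 0.075. The exercise arm is worse by more than 0.1 SD with probability P(Z > 0.1/0.075) ≈ 9%. In such trials (simulated, SD 0.5/0.75/1.0) subtype-only power was 78%, 77% and 73%, against 88%, 92% and 91% with adjustment. The mean subtype-only pCR difference was 8.9, 8.3 and 8.0 points where the truth is 10. With 3,000 trials per scenario, about 270 fall in this group, so these power figures carry an error of roughly 2 to 3 points.

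**7. Room for the parameters.** Expected pCR events: 0.30·356 + 0.40·356 ≈ 249. With grade (2), Ki67 (1), PR (1), cT (2) and cN (2) added to treatment (1) and subtype (3), there are 12 parameters, or about 21 events each.

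**The case against.** The strongest reply is that nothing here is wrong. The protocol states a principle (adjust for the stratification factors), follows it, and already includes the one predictor whose strength the documents quantify. The test holds its type I error, and under the assumed mix the planned model has about 88% power against a target of 80%. The documents give no within-subtype effect for grade, Ki67, PR, cT or cN; with no or weak effect, no gain is detectable. A separate statistical analysis plan may also add covariates. All of this stands, except that the protocol itself fixes the primary model, and its rationale covers stratification factors and small centres without giving a reason to omit fully available tumour features.

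Three stronger readings are tempting and not supported:
- A reader might infer that the plan sacrifices precision. For the planned effect measure the opposite holds: the standard error of the log odds ratio rises with each prognostic covariate.
- A reader might infer that chance imbalance biases the planned estimate. Over repeated randomisations it does not, and the planned confidence interval allows for it. The benefit of adjustment applies to the particular trial in which an imbalance occurs.
- A reader might infer that the RCB, RECIST and Cox models need the same covariates. No gain was calculated there, and the count of pCR events says nothing about them. The protocol expects few deaths and says that the trial is not powered for survival. In the ordinal models each covariate brings another proportional-odds assumption, and in the nominal fallback eight added terms become 8 × 3 = 24.

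**Conclusion.** A free improvement with a modest gain. The primary model is valid and reaches its stated power. Prespecified adjustment for grade, Ki67, PR, cT and cN would change power by roughly 0 to 5 percentage points at 712 patients: about 0 to 1 point for no to moderate prognostic value in the four-covariate simulation, and 4 to 5 points only if the features are strong within subtype. There is essentially no loss if they prove uninformative. Type I error stays near 5%.

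The second benefit is protection against chance imbalance through covariates chosen in advance. The price is an odds ratio conditional on more factors, with a slightly larger standard error on the log scale.

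The existence of the data rests on the eligibility criteria. The size of the gain rests on the assumed subtype mix, covariate distributions and within-subtype effects.

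**What to change.** Under Primary endpoint (pCR), before any outcome data by arm are seen, specify the primary analysis as logistic regression adjusted for biological tumour type, tumour grade, Ki67, PR status, cT and cN, all as recorded before randomisation. State the coding in advance, including the form in which Ki67 enters. Keep the subtype-only model as a supportive analysis. If a pCR difference is to be reported alongside the odds ratio, standardise it from the adjusted model, since that is where the gain in precision appears. Leave the RCB, RECIST and Cox models as planned.

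The cost is a short text change with no new data and no additional patients. The report must make clear that the odds ratio is conditional on the longer covariate list.
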